## Abstract

**Background:**

Ageing is associated with a decrease in physical activity. This decrease particularly occurs during specific transitional life stages. Especially during adolescence and young adulthood a steep decrease in physical activity is observed. Inactive people are often not aware of their inactivity. Providing feedback on the actual physical activity level by an activity monitor can increase awareness and may in combination with an individually tailored physical activity advice stimulate a physically active lifestyle.

**Methods:**

In a randomized controlled trial the effectiveness of providing an activity monitor in combination with a personal physical activity advice through the Internet will be examined. Outcome measures are level of physical activity, determinants of physical activity, quality of life, empowerment, aerobic fitness and body composition. Participants are relatively inactive adolescents and young adults who are measured at baseline, after 3 months intervention and 5 months after the end of the intervention. In addition, facilitating and hindering factors for implementation of the intervention will be investigated.

**Discussion:**

The use of a personal activity monitor in combination with web-based assisted individually tailored health promotion offers a good opportunity to work interactively with large groups of adolescents and young adults and provide them with advice based on their actual activity level. It has great potential to motivate people to change their behaviour and to our knowledge has not been evaluated before.

## Background

### Realization of the research project

In 2002, PAM B.V. (Doorwerth, The Netherlands) introduced a commercially available innovative product and concept to promote physical activity. This concept consists of a physical activity monitor (PAM) as well as a specially designed website (PAM COACH) which gives personalized physical activity advice, based on the amount of physical activity measured by the physical activity monitor. After consultation with PAM B.V. ([name]), the VU University Medical Centre (VUmc) and the National Institute for Public Health and the Environment decided to evaluate this concept by scientific research. An application for funding was made and granted by The Netherlands Organization for Health Research and Development (ZonMw), a non-profit organization. In order to conduct the PAM project, PAM B.V. sold the required PAMs to VUmc and facilitated access to the PAM COACH website, and provided us with technical PAM support. PAM B.V. was not a partner in the research proposal and in the further execution and processing of the study. The PAM project started in 2003 and will end mid-2006.

### Arguments for publishing the design of a study protocol

This article describes the design of a randomized controlled trial (RCT). Although the RCT has started already, no results are known at this point. Publishing the study design before the results are available has some important advantages. It offers the possibility to elaborate on the content of the intervention. This broad information gives users of similar interventions insight in the practicalities of the intervention and may promote wider implementation of the intervention if proven effective. Furthermore, it offers the opportunity to consider the methodological quality of the study more objectively, irrespective of the results.

### Introduction

The positive health benefits of physical activity in people of all ages have been extensively studied and are now commonly accepted. There is compelling evidence that regular physical activity increases physical functioning, aerobic fitness and quality of life and favourably influences many risk factors for chronic diseases, such as coronary heart disease, colon cancer and type 2 diabetes mellitus [1,2]. Nonetheless, people in industrialized countries continue to reduce their energy expenditure in daily living and at work. Leisure time activities have become more sedentary, with television watching, playing videogames, and personal computer usage among the most popular sedentary pastimes [3,4]. Especially during adolescence and young adulthood a steep decrease in physical activity is seen [5-7]. Adolescents are recommended to perform at least moderate physical activity with a minimum of one hour a day [8,9]. In 2004, only 31% of the male and 18% of the female adolescents (12–17 yrs) in the Netherlands complied with this guideline, according to data of the StatLine of the Dutch Central Bureau of Statistics [10]. Adults are advised to perform at least moderate physical activity for a minimum of 30 minutes on at least five days of the week. In 2004, only 50% of the Dutch young men and 55% of the women (25–35 yrs) were sufficiently active according to this guideline. An effective intervention to promote physical activity in these specific age-groups could therefore provide enormous health gains [11]. In a cross sectional study [12] among 2600 adults in the Netherlands was shown that 60% of the people that did not meet 30 minutes of physical activity on at least five days of the week, overestimated their own physical activity levels. Hence, feedback on the actual amount of physical activity per day may overcome this problem of poor self-evaluation and thereby positively affect the physical activity level among inactive persons.

One way to provide direct feedback on the actual amount of physical activity is via a physical activity monitor. Physical activity monitors can be worn without major inconvenience, requires little effort of the user and are compatible with most daily activities, making it a practical and socially acceptable measure of physical activity. Moreover, in a study of Rooney et al. [13], an increase in awareness of daily activity and increased physical activity was found, after wearing a pedometer for eight weeks.

Another way of providing feedback is via the computer. Computer-tailored interventions showed to be an acceptable, feasible and effective tool for promoting physical activity [14,15]. Furthermore, in a study of Brug et al. [16] computer tailored information appeared to have a greater impact in motivating people to change their diet than a general advice. The computer tailored information was more likely to be read, remembered and experienced as personally relevant compared to standard materials.

Internet websites enable to deliver tailored physical activity information on participants' desired moments and have the capability to easily reach large numbers of participants. Therefore, web based tailored interventions for physical activity could have great potential. However, until this point there is little evidence about the effectiveness of web-based-tailored interventions on physical activity. In an eight-week pilot intervention study of McKay [17], the intervention group received personalized feedback, received and could post messages to an on-line "personal coach", and were invited to participate in peer group support areas. This study found an overall moderate improvement in PA levels within both intervention and control conditions, but no significant between-group difference.

In our study we hypothesize that the use of a personal activity monitor (PAM) combined with an individually tailored physical activity advice will increase awareness and subsequent physical activity among inactive people. PAM-users will receive personal feedback and a personal physical activity advice. The use of an activity monitor in combination with a personal physical activity advice through the Internet is an innovative intervention that has not been evaluated before. The intervention is assumed to be attractive for adolescents and young adults. To date 84% of Dutch adolescents (12–17 yrs) and 71% of young adults (25–34 yrs) make use of the internet on a computer at home [18]. This underlines that the current generation of young people is accustomed to using computers and the Internet, and have the skills to participate in this intervention. In this randomized controlled trial the effectiveness of the PAM-accelerometer (PAM. B.V.) in combination with an individually tailored physical activity advice is evaluated in relatively inactive adolescents (12–18 yrs) and young adults (age 25–35 yrs).

## Methods

### Study design

The physical activity level of 300 adolescents and 300 young adults is monitored for two weeks. Based on these two monitor weeks, fifty percent relatively inactive adolescents and young adults are selected for the intervention study. In a randomized controlled trial (RCT) the effectiveness of a distributed PAM activity monitor coupled to a tailored physical activity advice through the Internet among adolescents and young adults in stimulating physical activity will be evaluated Effects on determinants of physical activity, quality of life, empowerment, aerobic fitness and body composition will be examined as well. In addition, a process evaluation is performed. See figure 1 for the flow chart of the participants.

**Figure 1 F1:**
[figure not shown]
Participant flow chart.

### The PAM-concept

The Personal Activity Monitor (PAM, model AM101, 28 gr, 59 × 43 × 10 mm, PAM B.V.), is a uni-axial accelerometer in the vertical direction and comparable to the accelerometer developed by Meijer et al. [19]. The PAM can be attached easily to a belt and is worn on the right hip. The PAM produces a cumulative score, which is a proxy measure of total daily (24 h) physical activity. The PAM score is displayed continuously on the PAM. Via a docking station, which must be connected to a computer with an Internet connection, the user can upload his personal PAM scores through PAM software to the COACH database any time of the day. The COACH database is part of the COACH website. At first login on the COACH website, the users register themselves by filling out a form with personal data (i.e. height, weight) and a onetime brief questionnaire with 10 yes-no questions (e.g. Do you think you are able to walk to your work when it is raining?). Entering the COACH website, the user is asked to formulate an activity goal along with the COACH, based on the users' PAM score and age. On every subsequent login the COACH website presents all the collected PAM scores in orderly graphs per day which is supported by practical information on user preferred activities (e.g. daily an extra 60 minutes walking, or 25 minutes running, or 20 minutes playing squash). In addition, the user receives on subsequent logins tailored feedback on determinants of physical activity based on the answers of the onetime questionnaire at registration. Next to the feedback on the COACH website, the users can easily monitor their progress in daily physical activity by reading their score on the display of the PAM itself. Users can thus compare their progress with their set personal activity goal. Furthermore some features are changed with the cooperation of Pam B.V at the original COACH website in aid of the intervention. Unlike the original COACH website, the intervention COACH website will neither formulate a weight goal, nor give nutritional advice. Furthermore, general practical advices to implement physical activity in daily life are added to the site. A different advice is given on each subsequent login.

### Study population

The study includes apparently healthy adolescents, aged 12 to 18 years old and young adults, aged 25 to 35 years old. Inclusion criteria are ability to walk, speak Dutch and not being pregnant. The study protocol is approved by the Medical Ethics Committee of VU University Medical Centre before the start of data collection. The adolescents will be instructed to take the consent materials home to their parents, read the materials with their parents, and return the consent, signed by both the parent and the adolescent if they are willing to participate in the study. Informed consent will also be requested from the young adults.

### Recruitment

#### Adolescents

Adolescents will be recruited from high schools in the surroundings of Amsterdam. Enrolling students at a school site has the following benefits:

1. All ages in the age-range from 12 to 18 years are represented;

2. Students have fixed classes according to a fixed time schedule which facilitate the measurements;

3. Different educational levels can be selected;

4. At school students have access to computers with internet at school;

Schools in the surroundings of Amsterdam with a minimum of 1000 students and with different educational levels are approached by phone. In all schools first the physical education (PE) teacher are contacted. If the PE staff is interested, an appointment is made for a personal interview. The PE teachers are asked to assist with the recruitment and facilitation of the outcome measurements. After approval of the school board and the PE section, the project is presented to the children during the PE-class by the study staff and the adolescents receive an information leaflet with consent materials. The adolescent and his parents had one week to hand in the informed consent forms, which are collected at the day of the first measurement for the selection of the intervention. At each school one regular school day in the week is selected to reach different ages and educational levels.

#### Young adults

Young adults are recruited from worksites in the surrounding of Amsterdam. It was decided to include office workers, since they perform mostly sedentary work and are constrained to their work place. This simplifies recruitment of the participants and measurements at the worksite. Companies with mainly office workers are selected, and either their occupational health and safety coordinator or an employee of human resources is approached by phone. If the company is interested, a face-to-face meeting is arranged. If all stakeholders are informed and have given their approval, information on the project is distributed to the employees according to the companies' policy. The company is asked for assistance with the recruitment and to facilitate the measurements. Every employee receives identical information about the project; i.e. a recommendation letter of the occupational health and safety coordinator and an information brochure with a consent form. The consents are collected at the day of the first measurement. The measurements of the selection for the intervention as well as the measurements of the intervention take place during working hours at the worksite.

### Selection for intervention

The target group for the intervention study is relatively inactive subjects. In order to select these subjects, 300 adolescents and 300 young adults are asked to wear a PAM accelerometer during their daily activities for two weeks. The PAM display is blinded during this period. After this two weeks-period all participants are asked to fill in a short physical activity questionnaire (an adapted version of the SQUASH questionnaire; [20]). The adolescents and young adults are divided in an active and inactive group by means of a combined physical activity score. Physical activity data of the PAM and the AQUA are divided in four quartiles, stratified for educational level. The first quartile includes the most inactive subjects. For each subject the quartile-numbers of both the PAM and AQUA will be summed up. Those who are classified as 'inactive' (combined score lower than 5) will be invited for participation in the intervention study. When the combined score is five, the AQUA quartile plays a decisive role (See figure 2)

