### Intervention

The subjects classified as relatively inactive will be invited to take part in the intervention study. For the intervention study they will be required to fill in a questionnaire and to participate in physical measurements (i.e. baseline measurements). After completion of the baseline measurements the participant are randomly assigned to the intervention or the control group. Participants in the intervention group receive the PAM monitor and have access to their personal website (COACH) for a 3-month period. The participants are given written and verbal instructions and practical demonstrations on how to wear the PAM and how to use the COACH. Special attention is paid to:

1. placing the PAM on the hip;

2. connecting the docking station to the computer;

3. installing the software on the computer;

4. registering and logon to the PAM COACH website;

5. setting a PAM goal and reading the results at the COACH website.

The control group receives a single written information brochure with general recommendations and guidelines for physical activity. Telephone numbers and an e-mail-address are provided in case questions arise. At each intervention site at least one computer with PAM software is arranged.

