### Measurements

The primary outcome of the intervention study is the level of physical activity measured by questionnaire. Secondary outcomes are determinants of PA, quality of life, empowerment, aerobic fitness and body composition. A compact questionnaire is constructed to maximize the response and minimize time spent filling in the questionnaire. All measurements are performed at baseline and after 3 months of intervention. Five months after the 3 months intervention only the questionnaire is repeated.

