### Statistical analysis

The primary analysis will be a comparison of the change in physical activity (PA) between the intervention and control group following the "intention to treat" principle. To adjust for the dependency between observations of subjects from the same school and class or company, multilevel analysis will be performed. Intention to treat analyses will also be performed for the secondary outcomes; determinants of physical activity, quality of life, empowerment, aerobic fitness and body composition. Pre-planned subgroup analyses will be performed for adolescents and adults and separate for gender. Where appropriate, adjustments will be made for differences at baseline values. Per protocol analyses will also be carried out.

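### The adjustment rule waits for observed baseline differences and does not name the screening AQUA or PAM score as covariates: an optional, small gain in precision

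*Protocol article*

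**What the plan says.** All statements are in the Methods of the protocol article.

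- **Selection for intervention.** "300 adolescents and 300 young adults are asked to wear a PAM accelerometer during their daily activities for two weeks". The display is blinded, and the AQUA follows: "After this two weeks-period all participants are asked to fill in a short physical activity questionnaire". The use stated for these data is eligibility: "For each subject the quartile-numbers of both the PAM and AQUA will be summed up", and the sum picks out the relatively inactive half.
- **Intervention.** Those selected are measured again: "For the intervention study they will be required to fill in a questionnaire and to participate in physical measurements (i.e. baseline measurements". Allocation comes last: "After completion of the baseline measurements the participant are randomly assigned to the intervention or the control group".
- **Measurements.** "The primary outcome of the intervention study is the level of physical activity measured by questionnaire".
- **Statistical analysis.** "The primary analysis will be a comparison of the change in physical activity (PA) between the intervention and control group", by intention to treat, in a multilevel model. On covariates, the section says: "Where appropriate, adjustments will be made for differences at baseline values".

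So each randomised participant has a screening AQUA, a baseline questionnaire and two weeks of blinded accelerometry, all recorded before allocation. The screening scores are neither listed as covariates nor ruled out.

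**The concern.** The stated rule has two weaknesses. It makes adjustment depend on differences seen at baseline, and it leaves the decision open by applying only where appropriate. In a randomised comparison, a covariate earns its place by predicting the outcome, not by being unbalanced. Read literally, the rule would leave out a strongly prognostic variable that happened to be balanced, although adjusting for it would still reduce residual variance.

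The outcome is a single seven-day recall, which is a noisy measure of usual activity, and the plan counts on 50 analysed participants per group in each age group. A second recall and an objective score taken before randomisation plausibly carry some further information, and they are already in hand. What is at stake is a modest amount of precision. The validity of the comparison is not affected.

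**Working it through.** **The plan's own figures.** The article gives no figure for precision gained by adjustment, so there is nothing to reproduce on that point. Its sample size of 50 per group is for a 20-point difference in a proportion and cannot be confirmed, because no control proportion is given. A two-sided calculation needs 49 per group at 5% v 25% and 62 at 10% v 30%. The dropout step does reproduce: 100/(1 − 0.33) = 149.3, about 150 per age group. Neither figure is contested here.

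**Inputs.** The timing and availability of the scores come from the sections above. The documents give no correlations, so these are assumed: r = 0.4–0.7 between AQUA occasions, and 0.2–0.4 between PAM and AQUA.

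**Step 1: formulas before selection** (variance in units of SD², equal correlation r between all AQUA occasions).

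- Unadjusted change score: 2(1 − r)
- Adjusted for baseline AQUA: 1 − r²
- Adjusted for baseline and screening AQUA: 1 − 2r²/(1 + r)

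At r = 0.5 these are 1.000, 0.750 and 0.667. The last divided by the second is 0.889.

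**Step 2: apply the selection rule.** Selecting on the screening scores narrows their range and reduces what they can add. One million multivariate-normal subjects were simulated and the half chosen by the quartile-sum rule was kept. Ties at a score of 5 were resolved by retaining AQUA quartiles 1–2, which is an assumption because Figure 2 is not shown. At r = 0.5 and PAM correlation 0.2:

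| Analysis | Residual variance |
|---|---|
| Unadjusted change | 0.998 |
| Baseline AQUA | 0.702 |
| Baseline AQUA, screening AQUA and PAM | 0.660 |

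Baseline AQUA alone removes 1 − 0.702/0.998 = 30%. The two screening scores remove a further 1 − 0.660/0.702 = 6%.

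**Step 3: vary how well the screening AQUA predicts follow-up.** It lies further from follow-up than the baseline AQUA does, so an equal correlation is a favourable assumption. The table gives the further reduction beyond baseline AQUA.

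| Screening-to-follow-up correlation | r = 0.4–0.7 | r = 0.7 only |
|---|---|---|
| Equal to r | 4–11% | 11% |
| r − 0.1 | 2–6% | 3–4% |
| r² (serial decay) | 1–8% | 1–3% |

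**Step 4: cost.** Two extra covariates inflate variance by roughly 2/n: 2/100 = 2% within one age group, or 2/200 = 1% with both age groups together.

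**Step 5: net effect within one age group.** At the top, 0.889 × 1.02 = 0.907, a net reduction of about 9%. At the bottom, 0.99 × 1.02 = 1.01, so the gain is cancelled. Before this cost, a variance ratio of 0.889 corresponds to about 45 per arm instead of 50, or power of about 84% instead of 80%. A ratio of 0.99 leaves both practically unchanged.

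**The case against.** The strongest objection is that this is a condensed article. A covariate list is commonly left to the full protocol or analysis plan, which is not shown, and the reference to baseline values could be read to include the screening scores or to mean ordinary baseline adjustment. A reader might infer that the screening data are never used, or that precision is thrown away. The documents do not support this. The scores decide eligibility, and no sentence excludes them from the analysis. That objection stands, so the point is confined to the adjustment rule that the article does state.

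A reader might also suspect bias, because participants are selected on low scores. Regression to the mean after selection affects both randomised arms alike, and leaving out a prognostic covariate does not bias the comparison. That stands too.

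Third, the increment is small and rests on assumptions. A figure of 4–11% holds only if the screening AQUA predicts follow-up as well as the later baseline AQUA does. This is correct, and the range has been widened to 1–11% for that reason.

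Finally, three extensions lack support. A missing-data indicator for PAM would have little or no use, since selection already requires both scores. Using the same covariates for all secondary outcomes was not computed. Nor was any benefit for handling the expected 33% dropout.

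What remains is that a rule triggered by observed differences is a poor way to choose covariates, and that fixing them in advance costs almost nothing.

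**Conclusion.** The point holds as an optional efficiency improvement. The stated rule makes adjustment depend on observed differences, and it does not name two plausibly prognostic measures that every selected participant has before randomisation.

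The main gain is from always adjusting for baseline AQUA, about 30% of residual variance against an unadjusted change score in the r = 0.5 example. The two screening scores add about 1–11% beyond that, for a cost of about 1–2%. At the low end there is no net gain.

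These figures rest on the assumed correlations, normality, a continuous outcome and the assumed tie rule, and they ignore clustering. The article sizes the trial on a proportion and plans a multilevel model, so the equivalent sample sizes and power are only indicative.

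**What to change.** In the Statistical analysis section, replace the adjustment sentence with a fixed rule: the primary multilevel model always includes baseline AQUA, with the screening AQUA score and the mean two-week screening PAM score as prespecified covariates, whether or not the groups differ on them. Change can remain the stated outcome, because with baseline AQUA in the model the treatment estimate is the same for change as for the follow-up value. If only part of this is adopted, unconditional adjustment for baseline AQUA matters most.

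The cost is one sentence of wording and two degrees of freedom. No new data are needed.
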